# Reducing the burden of orthodontic care for children with clefts: evaluating the effectiveness of pre-alveolar bone graft orthodontics in unilateral non-syndromic cleft patients (PABO study)— A study protocol for a multicentric randomised controlled trial

**DOI:** 10.1186/s13063-021-05505-0

**Published:** 2021-08-28

**Keywords:** Pre alveolar bone graft, Alveolar bone graft. ABG, Pregraft orthodontics, Cleft palate, Cleft alveolus, SABG, Cleft orthodontics

## Abstract

**Background:**

An alveolar cleft commonly affects 75% of cleft lip and palate patients. While it is common practice to provide a course of orthodontic treatment before alveolar bone grafting, there are no previous high-quality studies reporting on the benefits of this type of treatment.

**Aim:**

The aim of the study is to evaluate the effectiveness of pre-alveolar bone graft orthodontics for unilateral non-syndromic cleft palate patients.

**Method:**

The PABO trial is a multicentric, parallel, two-arm, single-blinded randomised controlled trial. The inclusion criteria include unilateral cleft alveolus patients requiring bone graft and between the age group of 8 and 13 years with erupted upper central incisors. Participants will be recruited at three centres across India. Participants will be randomised to orthodontic treatment or no orthodontic treatment group. Both groups of participants will have alveolar bone graft surgery and will be followed up for 6 months after surgery. The primary outcome will be the success of the alveolar bone graft measured by anterior oblique radiograph and secondary outcomes include quality of life, cost analysis and quality of the dento-occlusal outcome. Data analysis will be carried out by an independent statistician at the end of the study.

**Discussion:**

This study is the first to evaluate the effect of orthodontics on alveolar bone graft success. The increased burden of care for these patients with multiple treatments required from multiple specialists from birth to adult life highlights the need for reducing unnecessary treatment provision.

**Trial Registration:**

Clinical Trials Registry – India, CTRI/2020/10/028756. Trial prospectively registered on 29 October 2020.

.

## Background

Cleft lip and palate (CLP) are among the most common congenital malformations with an overall incidence of around 1 in 700 individuals newborns [1], and as a result, between 27,000 and 33,000 children in India are born with clefts every year [2]. CLP is accompanied by a wide variety of dental and skeletal anomalies, which have a long-term impact on the patient’s facial aesthetics, function and self-esteem. CLP affects a range of anatomical areas, and the optimal management of a child with cleft demands an organised multidisciplinary effort involving otolaryngology, plastic surgery, maxillofacial surgery, orthodontics, speech and language therapy, audiology, paediatrics, nursing, genetics, psychology, and social work. Despite general progress in medical care, cleft lip and palate and related craniofacial anomalies have largely remained ‘orphan’ conditions, falling between several main disciplines. Treatment provision lacks a firm evidence base and most published research has been uncoordinated. The care for these children is marked by controversies with multiple protocols concerning treatment [3]. Additionally, the care for this group of children is being delivered in a fragmented way through several centres in India [2]. In a previous study looking at the burden of orofacial clefting (OFC), it has been reported that a total of 79,430 cleft patients had unmet treatment needs which accounted for 18.76% of the total Indian cleft population [4].

An alveolar cleft commonly affects 75% of cleft lip and palate patients [5]. The cleft may influence the position of the teeth and the dental arches, cause speech problems, exacerbate facial asymmetry, and result in a lack of bone support for the anterior teeth [6]. It is now standard practice to correct this problem by bone grafting the cleft alveolus before the eruption of the permanent canines [7]. It is also common clinical practice to provide a course of orthodontic treatment to correct any discrepancy between the alveolar segments and widen the cleft alveolus to improve surgical access. While it is common practice to provide a course of orthodontic treatment before alveolar bone grafting, a recent systematic review of the literature reveals that most studies underpinning this procedure are retrospective analyses of case series [5]. Importantly, there has been no prospective randomised trial on the benefits and relative costs of this procedure. This has led to some diversity of practice in India with some Indian centres carrying out pre bone graft orthodontic treatment routinely, while others do not.

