## Rationale

A child undergoing pre-graft orthodontic treatment has to attend the Cleft Centre over a 6–15-month period, on amonthly basis and is also subject to the risks of orthodontic treatment, for example, dental decay, gingivitis, and root resorption [8]. It could be argued that this increases the burden of care for the child and parent and overall treatment costs, particularly if the treatment extends into the definitive phase of care. Furthermore, they have to undergo orthodontic treatment at an earlier age than their peers and may feel ‘set apart’ from their friends and classmates.

There is a serious lack of research in terms of comprehensive cleft care of UCLP patients at various stages of development in India. To our knowledge, there are no high-quality studies on pre alveolar bone graft orthodontics for cleft patients in India. Hence, this proposed study is aimed at evaluating the need for prealvoelar cleft orthodontics, reducing the burden and at the same time standardising and improving the quality of care for these patients.

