### Interventions

Orthodontic treatment will be provided for the treatment group. The treatment will involve fixed braces for the top teeth with or without expanders to widen the top jaw. The brace technique will be a clinical judgement and will be done in real-world setting. The treatment with a fixed brace can take up to 15 months. This will be followed by alveolar bone graft surgery to repair the cleft palate. The alveolar bone graft surgery will be standardised across all surgeons.

In the control group, no orthodontic treatment will be provided but the patients will have alveolar bone graft surgery.

The trial will be carried out in a real-world setting and the patient will not be prohibited from any other care during the trial.

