### Data collection

Data will be collected at the following points:
▪ T1: At the start of treatment/baseline▪ T2: 9 months from baseline▪ T3: Pre alveolar bone graft▪ T4: 3 months post alveolar bone graft▪ T5: 6 months post alveolar bone graft

Records, i.e., study models, intra-oral and extra-oral photographs and a oblique occlusal radiograph will be taken at each time point. A CBCT will be taken at T5 stage.

In addition, the following data will be collected from patients’ notes:
Number of attendances, including failed and cancelled appointmentsOverall treatment durationFrequency of appliance breakages, if anyAny other emergencies

Patients will be required to fill in the Quality of Life questionnaires (CPQ_8-10_) which will inform us how the appliances will affect them as part of the qualitative assessment. The CPQ_8-10_ is a validated questionnaire and has been used in other orthodontic trials.

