### Data analysis

Data will be analysed by an independent statistician. A detailed analysis will be planned before the final analysis of the trial. The main features of the statistical plan are mentioned here.

Data analysis will be carried out at the end of the study.

The primary outcome, Kindelan bone-fill index, is an ordinal measure and will be compared between groups using the Mann-Whitney test. Additionally, the outcome will be categorised as successful (grade 1) or unsuccessful (grades 2–4). The chi-square test will be used to compare the categorised outcome between groups.

Independent sample *t* test and 95% confidence intervals will be used for all continuous outcomes, for comparison between the groups. The dichotomous outcomes will be compared using chi-square test and the effect estimates will be reported using relative risk and 95% confidence interval. The qualitative outcomes will be compared using chi-square test.

A multivariable linear regression analysis will be carried out to assess the effect of pre-treatment complexity, gender and orthodontic treatment on the overall quality of alveolar bone graft success. The primary analysis will be on an intention-to-treat principle; the results of all subjects will be accounted for, regardless of the outcome of the treatment.

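### Grafting before canine eruption is given as standard practice, but eligibility, the control arm's time to graft and the named adjusted model do not take it up, so a null result would be hard to attribute

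*Protocol article*

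**What the plan says.** The Background describes accepted practice as "bone grafting the cleft alveolus before the eruption of the permanent canines". The other sections that bear on graft timing are these.

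- **Eligibility criteria.** Entry requires erupted upper central incisors and an age of 8 to 13 years. No inclusion or exclusion item mentions the canine.
- **Rationale.** A child having pre-graft orthodontics "has to attend the Cleft Centre over a 6–15-month period".
- **Interventions, orthodontic arm.** "The treatment with a fixed brace can take up to 15 months", and then: "This will be followed by alveolar bone graft surgery to repair the cleft palate".
- **Interventions, control arm.** "no orthodontic treatment will be provided but the patients will have alveolar bone graft surgery". No interval from randomisation to graft is given.
- **Data collection.** One schedule serves both arms. It lists "T2: 9 months from baseline" ahead of T3, the pre-graft visit; T4 and T5 are counted from surgery. At the visits, "study models, intra-oral and extra-oral photographs and a oblique occlusal radiograph will be taken at each time point".
- **Randomisation.** Stratified by gender only.
- **Data analysis.** The primary analysis is by intention to treat. A multivariable model is to "assess the effect of pre-treatment complexity, gender and orthodontic treatment on the overall quality of alveolar bone graft success".

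**The concern.** The protocol itself names a developmental limit for grafting and then does not carry it into the design. The age range is wide enough to admit children on either side of that limit. One arm has a course of braces before surgery, while the other arm's wait is undefined. Neither the stratification nor the named model includes age, canine stage or time to graft.

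Two things are at stake. First, stage at entry is likely to predict graft success, on the protocol's own account of when grafting is done, and leaving it out of the adjusted model gives up precision in a small trial. Second, the Discussion wants to know whether early orthodontics can be avoided without compromising the outcome. If the arms come out alike, one explanation is that orthodontics does nothing for the graft; another is that it helps but grafting later cancels the gain. Those explanations lead to different next steps, and nothing planned in the article would help a reader choose between them.

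**Working it through.** **1. Age at graft.** A child enrolled on the 13th birthday who has the full 15 months of braces is grafted at 13 y + 15 months = 14 y 3 months at the earliest. For the same child in the control arm, the documents give no figure. If grafted at once, the age is about 13 y. If the 9-month visit really precedes the pre-graft visit in both arms, it is at least 13 y 9 months. The extra wait in the orthodontic arm therefore cannot be calculated from the text.

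**2. The plan's own sample size.** Inputs from the sample size section: 60% against 25% success, 5% significance, 80% power. Two-sided, pooled variance, no continuity correction:

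n = [1.96·√(2 × 0.425 × 0.575) + 0.8416·√(0.60 × 0.40 + 0.25 × 0.75)]² / 0.35² = (1.370 + 0.550)² / 0.1225 ≈ 30.1, so 31 per group.

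This matches the stated 31. Power at 31 per group is 81.2%. The present point does not turn on this figure; it serves as a reference for step 5.

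**3. Children affected, simple assumption.** 72 recruited at 1:1 is 36 per arm. If 10–30% of the orthodontic arm pass canine eruption before graft: 0.10 × 36 = 3.6 and 0.30 × 36 = 10.8, or about 4–11 children. The 10–30% is an assumption; the documents give no eruption ages.

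**4. Children affected, explicit model.** Assume entry ages uniform over 8–13 years (60 months) and a single age at which the canine erupts, well inside that range.

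- Already past it at entry, in both arms alike in expectation: (13 − A)/5. For A = 12, 11 or 10 this is 20%, 40% or 60%, or about 14, 29 or 43 of 72 children.
- Passing it during a wait of D months: D/60. For D = 6, 9 or 15 this is 10%, 15% or 25%, or 3.6, 5.4 or 9 of 36 children.
- Excess over control when controls wait C months: (D − C)/60. With D = 15: 25% if C = 0, 10% if C = 9, and 0% if C = 15.

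Under these assumptions, variation in stage at entry involves more children than crossing during treatment in most of the cases shown, which is why the baseline covariate matters. The between-arm excess depends wholly on the unstated control wait.

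**5. Possible dilution.** Suppose controls are grafted at once and late grafting lowers success by an assumed 10, 20 or 35 percentage points. Orthodontic-arm success is then 0.60 − (D/60) × loss.

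| Wait | Loss | Success | Power at 31 per group |
|---|---|---|---|
| 6 months | 10 / 20 / 35 points | 59.0 / 58.0 / 56.5% | 79 / 76 / 72% |
| 15 months | 10 / 20 / 35 points | 57.5 / 55.0 / 51.3% | 75 / 68 / 57% |

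This is illustration only. The loss values are not in the documents. If the 60% planning figure comes from children who were themselves grafted after orthodontics, it may already contain some or all of this effect.

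**The case against.** The strongest reply has four parts. The Background sentence describes general practice and is not a trial rule, so an eligibility list that omits the canine does not contradict it; the surgeon and orthodontist assess each child, and entry requires that a graft be needed. The trial compares strategies in routine care, and any delay caused by braces is part of the strategy. The article is a condensed account that promises a more detailed analysis plan, and its complexity covariate is undefined and might include dental stage. Finally, no section says that grafting after eruption lowers the bone-fill grade.

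Much of this stands. There is no formal contradiction, and the size of any timing effect is unknown. What remains is that the article itself fixes the age range, the brace duration, the stratifier and the model covariates, and none of these is tied to the timing standard it cites.

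Two stronger readings are tempting and should be resisted. A reader might infer that only the orthodontic arm can be delayed. The text does not say so: no control interval is given, and the shared schedule places a 9-month visit before the pre-graft visit. A reader might also infer that canine stage goes unseen. It does not. Models, photographs and oblique films are taken at T1 and T3. The Data collection and Radiographs sections differ on whether a film is taken at T2, but agree on T1 and T3. What the article does not describe is a planned reading of those records for canine stage.

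**Conclusion.** The point holds as one about interpretability and precision. Age and canine stage at entry are outside both the stratification and the named adjusted model; time to graft is undefined for controls and may differ between arms; and a null result could not be assigned to orthodontics itself rather than to later grafting.

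A reader might go further and conclude that the comparison is confounded. It is not: randomisation balances stage at entry in expectation, and the intention-to-treat contrast estimates the effect of offering the orthodontic strategy, with whatever wait it brings. Nor do the documents support describing late grafting as an unreviewed, treatment-caused harm. No section quantifies such a harm, and the DSMB has a general remit for interim safety monitoring.

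The size is uncertain. The figure of about 4–11 of 36 orthodontic children rests on an assumed 10–30%, and the difference between arms tends to zero if controls wait a similar time. That canine stage is prognostic is inferred from the Background's timing standard and is not demonstrated in the documents.

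**What to change.** - The trial team should reconcile the Background, Eligibility criteria, Interventions and Data collection sections on graft timing, including what the schedule implies for time to graft in the control arm. No clinical rule is proposed here.
- Grade cleft-side canine eruption (unerupted, erupting, erupted) at T1 and T3 in both arms from the oblique films, models and photographs already planned.
- Add T1 canine stage, or age at T1, as a pre-specified covariate in the adjusted analysis.
- Report descriptively by arm the time from randomisation to graft and the number of children whose canine erupted before graft. Do not adjust for T3 stage or time to graft, because both follow allocation.

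The cost is some protocol wording, one grading item read from existing records, and one more covariate in a 72-child trial. No extra visit or radiograph is needed. The descriptive tables will not prove a mechanism, but they will show whether the two arms differed in timing at all, which is the first thing a reader of a null result would need to know.

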## Rationale

A child undergoing pre-graft orthodontic treatment has to attend the Cleft Centre over a 6–15-month period, on amonthly basis and is also subject to the risks of orthodontic treatment, for example, dental decay, gingivitis, and root resorption [8]. It could be argued that this increases the burden of care for the child and parent and overall treatment costs, particularly if the treatment extends into the definitive phase of care. Furthermore, they have to undergo orthodontic treatment at an earlier age than their peers and may feel ‘set apart’ from their friends and classmates.

There is a serious lack of research in terms of comprehensive cleft care of UCLP patients at various stages of development in India. To our knowledge, there are no high-quality studies on pre alveolar bone graft orthodontics for cleft patients in India. Hence, this proposed study is aimed at evaluating the need for prealvoelar cleft orthodontics, reducing the burden and at the same time standardising and improving the quality of care for these patients.

## Methods

### Aim

To aim of this study is to compare the effectiveness of pre alveolar bone graft orthodontic treatment with no orthodontic treatment for children with unilateral cleft palate requiring alveolar bone graft surgery.

### Objectives

To evaluate the effectiveness of pre alveolar bone graft orthodontic treatment for children with unilateral cleft palate.

### Null hypothesis

The use of pre graft orthodontics is no more effective than no orthodontic treatment for cleft alveolus patients.

### Design

Prealveolar bone graft Orthodontics (PABO) study is a 1:1 parallel group multicentre trial. Children aged between 8 and 13 will be randomised to either pregraft orthodontics group or no orthodontic treatment group. The study design is illustrated in Fig. 1.

**Fig. 1 Fig1:**
[figure not shown]
Schematics of trial design

### Study setting

The trial will be coordinated from Sree Balaji Dental College, Bharath Institute of Higher Education and Research, India. The trial will be conducted by cleft teams based in three centres across India. Criteria for the selection of sites are based on the previous experience in research and the volume of patients seen. The cleft team at each centre will include an orthodontist, cleft surgeon, paediatrician and cleft nurse.

### Eligibility criteria

Patients referred to cleft lip and palate centres will be included if they satisfy the below inclusion criteria:
Unilateral cleft alveolus requiring alveolar bone graftUpper central incisors erupted.Aged 8 and 13 years oldWritten informed consentOne care/parent must be a native language speaker of the state of residence.

Patients with any of the following will be excluded from the study:
Bilateral cleft palatePatients with syndromes or other medical conditionSubjects involved in any other orthodontic trialsInadequate oral hygiene

### Enrolment

The surgeon and orthodontist at each centre will assess the patient for inclusion and exclusion criteria. If the patient is identified as a potential patient, the parent/guardian will be invited, and information provided about the trial and the process of enrolment. The patient information sheet and consent form will be provided to the parent/legal guardian and they will then be given ample time to read and understand the forms and ask any questions. If the parent declines to participate, they will receive treatment as current practice and will receive the same level of support as patients participating in the trial.

If the parent/guardian agrees to take part, copies of the signed forms will be made, and one given to the parents.

Participants will be informed that they can withdraw from the study at any time without an explanation and their child’s care will not be affected.

### Randomisation

Once the consent is sought and the forms completed, the participant data will be entered on the central online randomisation system and the participant will be randomised using a secure online randomisation system to either the pregraft orthodontic group or no orthodontic treatment group, in a 1:1 ratio. The allocation sequence generation will be generated through the randomisation programme. The randomisation will be stratified on gender to get an equal number of males and females. The participants will be allocated by an independent researcher blinded to all the study data except to patient gender. Each participant will then be assigned a unique randomisation number.

### Interventions

Orthodontic treatment will be provided for the treatment group. The treatment will involve fixed braces for the top teeth with or without expanders to widen the top jaw. The brace technique will be a clinical judgement and will be done in real-world setting. The treatment with a fixed brace can take up to 15 months. This will be followed by alveolar bone graft surgery to repair the cleft palate. The alveolar bone graft surgery will be standardised across all surgeons.

In the control group, no orthodontic treatment will be provided but the patients will have alveolar bone graft surgery.

The trial will be carried out in a real-world setting and the patient will not be prohibited from any other care during the trial.

### Blinding

Due to the nature of the intervention, it is not possible to blind the investigator or the patient. The outcome assessor, however, will be blinded to the allocated group.

### Outcome measures

The primary outcome will be:
Success of alveolar bone graft assessed from CBCT and oblique occlusal (Kindelan method)

The secondary outcome measures will be:
Quality of the dento-occlusal outcome measured on study models using 10-year-old index scoresQualitative assessment using the validated quality of life questionnairesBreakagesQuality-adjusted cost analysis

The operator will record a patient as non-compliant if:
Subject refuses to wear the applianceBreakage of appliance for more than 3 timesMeasurement indicates a lack of clinical progress after 9 months of appliance wear

